#### Hopelessness

The Beck Hopelessness Scale (BHS) [102] is a self-report instrument that determines the extent of positive and negative beliefs about the future over the previous 7 days using 20 true-false statements. All statements are scored 0 or 1 with the total being calculated by summing the pessimistic responses for the items. General cut-off guidelines do not exist and it is recommended that cut-off scores should be based upon clinical decisions. The BHS has been shown to have good psychometric properties for application in clinical samples [103-105].

#### Interpersonal Problems

The Inventory of Interpersonal Problems (IIP) [106] is a 127-item self-report measure, which describes the types of problems that people experience in their relationships with others, and the level of distress associated with them. Items are divided in two sections: participants are asked to rate problematic behaviour that is hard for them to do (78 items) and behaviour that they are doing too much (49 items). The IIP provides a total score and scores on six or eight subscales. Higher scores indicate more interpersonal problems. Psychometric properties of the IIP were found to be good [106].

#### Cognitive Reactivity

During a depressive episode, an association is formed between depressed mood and dysfunctional thinking. This association may remain intact even when the depressive episode remits. The strength of this association is called cognitive reactivity [107]. The Leiden Index of Depression Sensitivity (LEIDS) is used to measure this cognitive reactivity on six subscales [108]. Psychometric qualities of this measurement are found to be good [108].

#### Rumination

The Ruminative Response Scale (RRS) [109,110] is a 22-item questionnaire that will be used to detect the responses to depressed mood that are focused on self, symptoms, or possible consequences and causes of mood. People are asked to indicate how often they think about certain things on a four point Likert-scale. The RRS shows good reliability and satisfactory validity [109,110].

#### Self-Esteem

The Self Liking and Self Competence Scale Revised (SLCS-R) [111,112] is a self-report questionnaire constructed to measure Self-Competence and Self-Liking, two dimensions of self-esteem. The SLSC-R contains eight items for each of the two dimensions. Items are rated on a 5-point Likert scale. The subscales scores can range from 8 to 40, with higher scores indicating higher self-competence or higher self-liking. Psychometric properties were found to be good [111].

### Economic Evaluation

#### Costs

A rudimentary analysis of the cost-effectiveness of CT and IPT will be conducted from a societal perspective. We will distinguish three cost categories: health care sector costs, costs for the patient and family, and productivity cost [113]. Healthcare costs and patient and family costs will be measured using a periodic retrospect health care consumption questionnaire designed by de Graaf et al. (2008) for use in the field of depression research [114]. This questionnaire is based on an existing cost diary [115] and retrospective cost questionnaires [116,117]. Containing 52 items, it measures the number and content of contacts with GPs, specialists, paramedics, alternative care, psychological care, hospital visits, medication, and self-help over a period of three months. To measure production losses we will use the patient modules (A-E) of the productivity and disease questionnaire (PRODISQ) [118].

#### Quality of Life measures

To measure the experiential impact of the disorder, the Work and Social Adjustment Scale (W&SAS) [119] will be used. This 5-item self-report scale examines to what extent the disorder impairs a person's everyday functioning. Items are rated on a 9 point Likert-scale, with higher scores indicating more severe impairment. Psychometric properties of the W&SAS are found to be good [119,120]. Furthermore, to measure generic quality of life of the patients on the basis of societal appreciation of health condition, the EuroQol [121] will be used. To measure quality of life in terms of impairments due to physical and mental health status, we will use the RAND-36 [122]. This 36 item questionnaire measures physical and social functioning, role restriction due to physical or emotional problems, mental health, energy, pain, and general health perception. The RAND-36 has shown to be a reliable, valid and sensitive measure [122].

### Other measures

#### Working Alliance

The past decades, it has become clear that therapeutic alliance is an essential element of the therapeutic process [123]. The stronger the collaborative and affective bond between patient and therapist, the larger the therapeutic change [124]. To measure this bond, the Working Alliance Inventory (WAI) [69,125] will be used. The questionnaire consists of 36 items rated on a 5-point Likert scale and will be filled out by both patient and therapist. The internal consistency of this instrument was found to be high. As has been mentioned earlier, all therapy sessions will be videotaped. Therapeutic alliance will also be assessed by rating a random selection of videotapes using the Observer version of the Working Alliance Inventory-Short (WAI-O-S) [71,72].

#### Genetics

There is evidence that the same genetic factors that appear to moderate the efficacy of different classes of antidepressants are also involved in aspects of cognitive functioning [126]. The same polymorphisms are also associated with reactions on aversive stimuli [127-129]. Because changes in regulation of emotions and cognitive processes are core elements in therapeutic approaches such as CT and IPT, we expect that the efficacy of these therapies is influenced by genetic variations in polymorphisms. Therefore, we will obtain genetic material at baseline (buccal cotton swabs).

### Analyses

Data-analysis will include intention-to-treat analyses, per-protocol analyses, change analyses and prognostic analyses. Analyses will include elementary head-to-head comparisons of the intervention groups as well as more complicated multivariate analyses (e.g., individual time series analysis, logistic regression analysis, multilevel analyses). Furthermore, in ancillary analysis, subgroups of the study sample according to symptom severity and DSM-IV classification will be examined for differential effects. In addition, we will determine the proportion of patients that show reliable and clinically significant improvement on the outcome measures. Our calculations will be based on the method of Jacobson and Truax [130] which prescribes that Clinical Improvement (CI) is based on both Reliable Change (RC), the extent to which the pre-to-post-difference score is reliable; and on Clinical Significant change (CSC), the extent to which post-treatment scores are clinically meaningful [131]. We will use chi-square tests to test the frequency differences in the RC, CSC, and CI between the three intervention groups.

Relapse (episode of MDD after remission) and recurrence (episode of MDD after recovery) in the course of follow-up (12 and 24 months) will be assessed using survival analysis (Cox proportional hazards regression). Furthermore, using multi-level mediation models, we will investigate various potential treatment mediators (psychological processes responsible for therapeutic change) to identify mechanisms of change. We will use the revised and expanded McArthur guidelines with a central focus on the temporal aspect [40,41]. Furthermore, we will use structural equation modelling to test the relative strength of the factors involved (path analysis), an approach already successfully applied by Oei and colleagues [48].

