**Methods:**

In a randomised trial we will compare (a) Cognitive Therapy (CT) with (b) Interpersonal therapy (IPT), and (c) an 8-week waiting list condition followed by treatment of choice. One hundred eighty depressed patients (aged 18-65) will be recruited in a mental health care centre in Maastricht (the Netherlands). Eligible patients will be randomly allocated to one of the three intervention groups. The primary outcome measure of the clinical evaluation is depression severity measured by the Beck Depression Intenvory-II (BDI-II). Other outcomes include process variables such as dysfunctional beliefs, negative attributions, and interpersonal problems. All self-report outcome assessments will take place on the internet at baseline, three, seven, eight, nine, ten, eleven, twelve and twenty-four months. At 24 months a retrospective telephone interview will be administered. Furthermore, a rudimentary analysis of the cost-effectiveness will be embedded. The study has been ethically approved and registered.

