### Sample size

To calculate the sample size of the CT and IPT group, we combined rudimentary findings from previous randomised trials, which resulted in a mean relapse/recurrence rate of 33% after two years of follow-up, compared to 67% following antidepressant medication and/or clinical management [28,29,31-33]. Based on these results, we assume a difference of 20% in relapse between CT and IPT. Using survival analysis (two-sided, α = 0.05, power = 80%), we calculated that 75 patients per treatment condition would suffice to detect this statistically significant difference rate in relapse/recurrence between the two conditions in the long term.

A waiting list condition is included to investigate whether the effects of CT and IPT exceed the outcome in patients who do not receive treatment, a finding that has been demonstrated in numerous previous studies [60-63]. A power calculation showed that 30 participants in the waiting list condition will be sufficient to detect a statistically significant difference between the two active conditions combined (CT and IPT) and the waiting list after eight weeks.

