### Clinical outcome measures

#### Beck Depression Inventory-II

The Beck Depression Inventory-II (BDI-II) [73,74] will be used as the primary outcome measure of depressive severity. The total score is the sum of the 21 items ranging from 0 to 63. Higher scores reflect more severe depressive symptoms. Several studies have shown that the BDI-II is a strong screening measure for depression [73-75].

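### Differential effects by symptom severity are to be examined in subgroups although a continuous baseline score is collected; banding costs the ancillary moderator test information, by an amount that depends on an unstated number of groups

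*Protocol article*

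**What the plan says.** The Analyses section places the question outside the main analyses, as an ancillary analysis in which "subgroups of the study sample according to symptom severity and DSM-IV classification will be examined for differential effects". It does not say how many severity groups there will be, where the cuts fall, which instrument defines severity, which outcome is meant, or whether the comparison is by an interaction test.

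A numeric severity score is available. For the BDI-II, the article states: "The total score is the sum of the 21 items ranging from 0 to 63". Table 1 marks the BDI-II at month 0, and also the QIDS. The section on randomisation and procedure places allocation after the baseline questionnaires, so the score is a proper pre-randomisation moderator.

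The Analyses section also names "more complicated multivariate analyses (e.g., individual time series analysis, logistic regression analysis, multilevel analyses", but does not tie any of these models to the severity question. The article gives no clinical, guideline or other reason for grouping severity, and no power figure for this analysis. The only sizing statement for the two active arms concerns relapse: "75 patients per treatment condition would suffice to detect this statistically significant difference rate in relapse/recurrence".

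**The concern.** Banding a continuous moderator treats all patients within a band as equally severe, and treats two patients just either side of a cut as different. If the CT-IPT difference changes gradually with severity, part of that gradient lies inside the bands and is discarded.

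A test of whether a treatment difference varies across patients has limited power in a trial of this size, which was sized for relapse and not for moderation. Reducing that power further makes a real dependence on severity easier to miss. A null subgroup result could then be read as showing that severity does not matter for the choice between CT and IPT.

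**Working it through.** The article gives no figure for this analysis, so there is nothing to reproduce. What follows measures the cost of grouping under stated assumptions.

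**Inputs from the article.** 75 patients in each of CT and IPT (Design of the study; Sample size); BDI-II collected at baseline (Table 1); severity examined in subgroups (Analyses).

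**Assumptions, not in the article.** Normally distributed baseline severity, a linear interaction, a two-sided 0.05 test, and an interaction that would have 80% power on the continuous score. That 80% is a reference point only; the article's own 80% belongs to the relapse comparison.

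**Step 1: information retained.** The retained share R is the squared correlation between the score and its group means.

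- Two groups cut at proportion q: R = φ(z_q)² / [q(1 − q)]. At the median, 0.3989² / 0.25 = 0.637.
- Three equal groups: the group means are −1.091, 0 and 1.091 SD, so R = (1.091² + 0 + 1.091²) / 3 = 0.793.
- Four equal groups: the means are ±0.325 and ±1.271 SD, so R = (0.325² + 1.271²) / 2 = 0.861.

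| Grouping | Retained | Lost |
|---|---|---|
| Median split | 0.637 | 36% |
| 30/70 split | 0.576 | 42% |
| 20/80 split | 0.490 | 51% |
| Three equal groups | 0.793 | 21% |
| Four equal groups | 0.861 | 14% |

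The shape of the distribution matters too. A median split loses 25% if severity is uniform, and about 34% to 35% if it is a normal score truncated below at 14, with assumed means of 28 to 32 and SDs of 9 to 10. In patient numbers, a median split of the 150 CT and IPT patients is worth 150 × 0.637 = 95.5 patients analysed on the continuous score; three equal groups are worth 150 × 0.793 = 119.

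**Step 2: power.** 80% power on the continuous score corresponds to a noncentrality of (1.960 + 0.842)² = 7.85. After grouping this becomes 7.85 × R.

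- *Groups compared as categories.* The arm-by-group test has k − 1 degrees of freedom, so power is the probability that a noncentral chi-square exceeds the 5% critical value.
- *Bands scored as a trend.* The test has 1 degree of freedom, so power = Φ(2.802 × √R − 1.960).

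| Groups | Noncentrality | Critical value | Power, categories | Power, trend |
|---|---|---|---|---|
| 2 (median) | 5.00 | 3.84 | 61% | 61% |
| 3 equal | 6.23 | 5.99 | 60% | 70% |
| 4 equal | 6.75 | 7.81 | 57% | 74% |

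More bands retain more information, but when they are compared as categories the added degrees of freedom offset the gain. With an uneven two-group cut, power is 57% at 30/70 and 50% at 20/80.

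**Step 3: check by simulation.** With 75 per arm, the interaction that gives 80% power is 2.802 × √(2/75) = 0.46 residual SD per SD of severity. In 4,000 simulated trials with no severity main effect, power was 78% for the continuous test and 59%, 58% and 55% for 2, 3 and 4 groups compared as categories. With a severity main effect of 0.5 it was 78% against 56%, 55% and 52%. A separate run of 6,000 trials, with a severity slope of 0.5 in one arm and the interaction added in the other, gave 78% for the continuous test, 52% for a median split and 65% for three bands scored as a trend. Banded tests do somewhat worse than the formula because severity differences within bands go into the residual. The formula therefore does not exaggerate the loss.

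**The case against.** The strongest objection is that the article never says severity will be cut in two. A reader might infer a high/low split and conclude that a third or more of the information is lost. The text does not support that: with three or four bands the loss is 21% or 14%, and if bands are scored in order the power loss is about 10 or 6 points. This stands, and the size must be stated as conditional.

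A second objection is that this is one clause in a condensed article, and that cut-points, instrument and form of test may be set out in a fuller plan not shown. This also stands, so their absence is not criticised here. It does not remove the point, because the use of severity subgroups is itself stated, and cut-points given elsewhere would confirm the grouping.

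Third, the article does not name the BDI-II as the severity measure for this analysis (the QIDS is also taken at baseline), nor the outcome. That limits how closely the remedy can be tied to a particular model, but not the principle.

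Finally, the analysis is ancillary, severity moderation is not among the main research questions, and the sample size does not rest on it. That is correct and limits the weight of the point.

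**Conclusion.** The point holds as a minor, inexpensive improvement. The plan groups a moderator that is already measured on a continuous scale and gives no reason for doing so. For an interaction with 80% power on the continuous score, comparing two to four equal groups as categories costs about 19 to 23 points of power; only a scored trend over three or four bands keeps the cost to about 6 to 10. These figures rest on normal severity, a linear interaction and a reference power of 80%, none of which the article states.

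Two stronger readings should be resisted. A fixed loss of a third or more does not follow, because it presumes a two-group split. Nor is there any threat to the main findings: the comparison of CT with IPT, the waiting-list comparison and the relapse analysis do not depend on this choice. The point does not extend to DSM-IV classification.

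**What to change.** For symptom severity, make the ancillary test the interaction between arm (CT versus IPT) and continuous baseline severity, with the BDI-II as the natural choice of score. Fit it in the regression or multilevel model used for the outcome concerned, include baseline severity as a main effect, and check for non-linearity, for example with a spline or quadratic term. Report the estimated CT-IPT difference with its confidence interval across the observed range of severity. Severity bands can remain as a descriptive display, and subgroups should be kept for DSM-IV classification.

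The cost is a sentence or two of analysis wording, with no new data and no additional patients. The one drawback is that a smooth form has to be assumed for the interaction, which the non-linearity check addresses.

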## Discussion

We presented the protocol of a study assessing the effectiveness, mechanisms of change and prevention of relapse/recurrence of CT and IPT for depression. While it is well known that both CT and IPT are effective treatments for depression, it is not entirely clear yet whether one therapy is superior to the other, especially in the long term. Furthermore, since response rates of both therapies are insufficient and the risk of relapse and recurrence is high, the challenge in contemporary depression research is the improvement of treatments to increase response rates and prevent relapse and recurrence. Studying the mechanisms of change in treatment might be a first step in improving every day clinical practice. Although in the past decades attention for mechanisms of change in psychotherapy has grown, this type of research is still in its infancy. It may be clear that there is a need for renewed methodologically well-considered research. With the current study, we hope to provide new insights in the issues stated above.

### Methodological Considerations

The current study has several strengths, including randomisation of patients to three conditions (CT, IPT and a waiting list condition). The used design (RCT) is not only the standard for the evaluation of effectiveness of psychiatric treatments, but is also very valuable in studying mechanisms of therapeutic change [132,133]. Furthermore, we follow the recommendation of Kazdin to measure multiple potential mediators simultaneously and to include multiple follow-up measures at various time-points throughout a 2-year follow-up period. We assess both mediators and outcomes before and after therapy. This repeated measures design will provide a unique opportunity to evaluate whether change in cognitions occurs in advance of, and is related to, reduction in symptoms. In addition, to our knowledge, we are the first to compare CT with IPT head-to-head for relapse prevention and assess the underlying mechanisms of change using both explicit and implicit measures in a treatment study of depression to examine the level of therapeutic changes. To conclude, we will use state-of-the art statistical techniques to analyze temporality, causality and mechanisms of change.

However, the current study also has a number of limitations. In spite of the fact that we consider many potential mechanisms, there probably will be important (latent) processes that are not assessed in the current study. Even though we will use analysing techniques to prevent these biases as much as possible, there still is a chance that results will be contributed to the measured variables, whereas they are actually caused by other latent variables.

### Conclusions

The current study will compare CT and IPT head-to-head in terms of effectiveness and the prevention of relapse. Furthermore, in order to investigate mechanisms of change, we will investigate potential mediators of CT for depression and test their specificity in comparison to IPT and vice versa. By including assessments on multiple time points in both the treatment- and follow-up phase, we try to investigate temporal relationships between change in potential mediators and outcome measures that are needed to identify causal pathways of therapeutic change. We will assess both specific and common treatment factors using both explicit and implicit measures. We hope to provide new insights in the mechanisms of change of CT and IPT for depression and through here contribute to the improvement of health care for adults suffering from depression.

## Abbreviations

ASQ: Attributional Style Questionnaire; BDI-II: Beck Depression Inventory, second edition; BHS: Beck Hopelessness Scale; BSI: Brief Symptom Inventory; CI: Clinical Improvement; CSC: Clinical Significant Change; CSPRS-6: Collaborative Study Psychotherapy Rating Scale - version 6; CT: Cognitive Therapy; DAS-A: Dysfunctional Attitude scale version a; DID: Diagnostic Inventory for Depression; DSM-IV: Diagnostic and Statistical Manual of Mental Disorders, fourth edition; IDS: Inventory of Depressive Symptomatology; IIP: Inventory of Interpersonal Problems; IPT: Interpersonal Therapy; LEIDS: Leiden Index of Depression Sensitivity; LIFE: Longitudinal Interval Follow-Up Evaluation; MDD: Major Depressive Disorder; PRODISQ: productivity and Disease questionnaire; QIDS: Quick Inventory of Depressive Symptoms; RC: Reliable Change; RCT: Radomised Controlled Trial; RIAGG: Regional Academic Community Mental Health Centre; RRS: Ruminative Response Scale; Sc-IAT: Single Category Implicit Association Test; SCID-I: Structural Clinical Interview for DSM-IV Axis I disorders; SCID-II: Structural Clinical Interview for DSM-IV Axis II disorders; SLSC-R: Self Liking and Self Competence Scale Revised; W&SAS: Work and Social Adjustment Scale; WAI: Working Alliance Inventory; WAI-O-S: Observer rated version of the Working Alliance Inventory Short
